##### Secondary outcome measures

The Scale of Experienced Stress (PSS-10) [60] is a scale made to measure stress levels and consists of 10 items. Higher scores indicate higher perceived stress.

The Academic Adjustment Scale (AAS) [61] is a nine-item scale that measures students’ academic adjustment levels. It has three subscales (three items on each): academic lifestyle, academic achievement, and academic motivation. It is widely used among permanent residents and sojourner students.

The Satisfaction With Life Scale (SWLS) [62] is a five-item self-report global measure of life satisfaction.

The Patient Health Questionnaire-9 (PHQ-9*)* [63] is a method used to assess levels of depressive symptoms. It consists of nine statements derived from the Diagnostic and Statistical Manual of Mental Disorders, Fourth Edition (DSM-IV) criteria for depressive disorder and an additional statement regarding the severity of existing symptoms in daily life.

The General Anxiety Disorder-7 (GAD-7) [64] is a measure used to assess levels of anxiety symptoms in generalized anxiety disorder (GAD) defined by the DSM-IV. The scale contains seven items related to GAD characteristics (feeling anxious, worrying too much, having difficulties relaxing, etc.).

The Five Facet Mindfulness Questionnaire (FFMQ-15) [65] is a 15-item self-report measure of mindfulness. It contains the same five facets as the longer form: observing, describing, acting with awareness, non-judging of inner experience, and non-reactivity to inner experience. It includes three items for each facet.

The Acceptance and Action Questionnaire (AAQ-II) [66] is the most widely used measure of psychological inflexibility and experiential avoidance. It consists of seven items rated on an 8-point Likert-like scale. Higher scores indicated greater psychological inflexibility. Developed initially as a direct measure of psychological inflexibility, later studies have highlighted how the AAQ-II could be more suited as an indicator of experiential avoidance [67].

The Self-Compassion Scale—Short Form (SCS-SF) [68] is a 12-item questionnaire designed to measure the capacity for self-compassion. The SCS-SF has two subscales: self-disparagement and self-care—six items on each. High levels of total score are characterized by high self-care and low self-disparagement.

The Cognitive Fusion Questionnaire (CFQ) [69] is a brief, unidimensional seven-item self-report measure of cognitive fusion.

The Perseverative Thinking Questionnaire (PTQ) [70] is used to measure repetitive negative thinking. It consists of 15 items, each associated with one of the process characteristics of perseverative thinking: (1a) intrusive (e.g. “Thoughts come to my mind without me wanting them to”), (1b) difficult to disengage from (e.g. “I can’t stop dwelling on them”), (2) unproductive (e.g. “I keep asking myself questions without finding an answer”), and (3) capturing mental capacity (e.g. “My thoughts prevent me from focusing on other things”).

The Warwick-Edinburgh Mental Well-Being Scale (WEMWBS) [71] is a measure of mental well-being. It consists of 14 items rated on a 5-point Likert scale. The higher the global score, the higher the level of mental well-being.

#### Daily diary assessment

The daily diary assessment will contain two parts.

The first part will be described as a daily diary of life events. In this part, participants are asked to recall all important events that happened that day. Using a 7-point Likert scale, participants will rate each event in terms of stressfulness and presence (how mindful they were). The second part contains questions evaluating daily well-being and depressogenic adjustment. All daily measures used in our study have been previously used in research [72, 73]. Each measure is based on a corresponding trait measure of the same construct, with items selected for appropriateness for daily administration and reworded. All daily items include the word “today.”

The following variables will be measured:

Depressogenic adjustment will be measured by three items based on Beck’s [74] triad.

Procrastination—measured by three items from the Pure Procrastination Scale [75].

Daily negative thinking—worrying and rumination. Daily worrying will be measured with three items taken from Meyer et al.’s scale [76]. Daily rumination will be measured with three items based on Trapnell and Campbell’s scale [77].

Emotional regulation—cognitive restructuring and emotional suppression. These variables will be measured using one item (each scale) from the Emotional Regulation Questionnaire (ERQ [78]).

Self-compassion—measured by three items from the SCS [68].

Daily affect—to be measured based on the circumplex model [79]. This model contains a combination of positive–negative, active–deactive emotions that produce four measures. Positive active affect is measured with ratings for feelings described as happy, proud, and excited/enthusiastic, and positive deactive affect is measured with ratings for those described as calm, satisfied, and relaxed. Negative active affect is measured with ratings for feelings described as upset, stressed, and angry, and negative deactive affect is measured with ratings for those described as sad, bored, and disappointed. Participants will be describing how they feel using a 7-point Likert scale.

#### Cognitive task

To measure the cognitive functioning of students, we will use an online version of the Stroop task [80] (color–word), adapted from Mead et al. [81]. It assesses cognitive flexibility and attention span. We will use the color–word condition and present on the screen names of colors printed with the ink of a different color (blue, red, green, yellow). The subject must name the color in which the stimuli are presented and disregard their verbal content by pressing the correct button. The color of the ink and the presented word are never the same. The Stroop test is a widely used measure in research on students’ mental health and cognitive functioning [82–84].

#### Adverse events

Post-treatment, adverse events will be assessed using a self-reported question, “Did you experience any negative effects during treatment? If yes, please give us further details” [85]. Then, the answers will be coded using unwanted effects checklist [86].

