## Methods/design

### Study design

This study is a parallel group randomized controlled trial (RCT). The participants will be allocated to one of three 6-week conditions: (1) online cognitive behavioural therapy, based on the unified protocol (iCBT-UP); (2) online progressive muscle relaxation training (iPMR, active control group); and (3) waiting-list control group (WLC). The last group will receive access to their chosen intervention after the waiting period (6 weeks). To help WLC participants maintain motivation, weekly emails will be sent to remind them of the study and to assess their mood. They will be instructed to contact the research team in instances of any crisis. At that point, they will be administrated by our team psychotherapist or psychiatrist and referred to an adequate service. Assessments will consist of questionnaires, a cognitive task and a study of daily diaries. All assessments will be administered through an online data collection platform delivered by organisers (Supporty.pl), occurring at (1) screening, (2) baseline (prior to randomization), (3) at the end of the 6-week online program (or waitlist period), and (4) 1 month after finishing treatment (for participants in the active intervention conditions). Daily diary studies will be carried out for entries in the first and again in the last week of the interventions. Cognitive task will be administered at baseline, at the end of 6 weeks of online intervention, and 1 month after finishing treatment. The study will follow SPIRIT guidelines (Standard Protocol Items: Recommendations for Interventional Trials) [47].

Figure 1 shows the trial design. The study protocol and informed consent have been approved by the Ethics in Research Committee of the Faculty of Psychology, University of Warsaw.

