### Interventions

The interventions are self-help digital programs that will be provided to participants through an online delivery platform. The participants will gain access to their randomly selected intervention via a self-generated password and email address. Access to programs will be provided for 8 weeks; the programs will be 6-week long. All conditions will include an anonymous chat function whereby participants can share opinions and ask the research team for help. The participants will also receive minimal therapeutic support. To this end, they will receive weekly emails introducing new program modules and containing motivating prompts. Additionally, once a week, they will receive a message on chat. The aim of this communication is to assess the mood of participants and provide brief feedback on their work to enhance their motivation.

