Module 5	Facing Physical Sensations	Participants learn about the effect of physical sensations. They induce physical sensations and learn how to tolerate and accept them
Module 6	Emotion Exposures	At the end, participants set a hierarchy of emotionally difficult situations and conduct emotion exposures
Summary		A brief summary of the content of all modules; relapse prevention

The iCBT-UP used in this study is an interactive intervention with text and audio materials, videos, quizzes, pictures, and gap-filling exercises. Each module consists of an introductory part—with a short video and text and an examination of previous knowledge—followed by a didactic component with activities to train new skills and personal stories where the participants become acquainted with the experiences of two students who are followed throughout the program.

We will recommend completing one module per week, but participants will have the option to complete the program at their own pace.

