	**Study period**						
	**Enrolment**	**Allocation**	**Baseline**	**During the 6 weeks interventions**		**Post assessment**	**Follow-up**
**Timepoint**	***-t***_***1***_	**0**	***t***_***1***_	***Daily Diaries week (1–7 day of intervention)***	***Daily Diaries week (36–42 day of intervention)***	***t2*** ***(1 day after the intervention)***	***t3*** ***(30 days after the intervention)***

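### The only checklist-coded negative-effects question falls at about day 43, but programme access runs to day 56, so effects of late module work may not be recorded by it

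*Protocol article*

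**What the plan says.** The Adverse events section of the protocol article states: "Post-treatment, adverse events will be assessed using a self-reported question". The question asks about negative effects during treatment, and the answers are coded with an unwanted effects checklist. Governance and oversight of the trial repeats the post-treatment timing. In Table 3 the adverse-event row has one mark, under post assessment (t2). Its follow-up (t3) cell is empty, whereas the IADQ, PHQ-9, GAD-7 and the other questionnaires are marked at both t2 and t3.

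Study design places the post-treatment assessment "at the end of the 6-week online program (or waitlist period". Table 3 describes t2 as "1 day after the intervention", puts the last diary week on days 36 to 42, and sets t3 at 30 days after the intervention.

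On access, the Interventions section says: "Access to programs will be provided for 8 weeks; the programs will be 6-week long". For iCBT-UP the recommendation is weekly ("We will recommend completing one module per week"), but "participants will have the option to complete the program at their own pace". Table 1 describes Module 5 as "They induce physical sensations and learn how to tolerate and accept them" and Module 6 as "At the end, participants set a hierarchy of emotionally difficult situations and conduct emotion exposures".

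Three other sources of harm information are described: weekly chat contact to assess mood and risk, a crisis pathway, and counts of deterioration and non-response on the outcome questionnaires.

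**The concern.** The design allows treatment to continue after the one occasion on which negative effects are asked about and coded. The modules that a slower iCBT-UP user would still have to do are the last two, which deliberately provoke bodily sensations and emotionally difficult situations. These are modules for which a reader of the harms table would want the record to be complete.

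At stake is the completeness of the coded negative effects among users who are behind. The primary and secondary efficacy comparisons are not touched.

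**Working it through.** The protocol gives no figure for this point, so there is none to reproduce. The check is calendar arithmetic, with day 1 taken as the first day of access (an assumption).

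**Calendar**
- End of the 6-week programme: 6 × 7 = day 42. This agrees with the last diary week, days 36 to 42.
- t2, one day later: 42 + 1 = day 43.
- End of access: 8 × 7 = day 56.
- t3: 42 + 30 = day 72.
- Access remaining after t2: 56 − 43 = 13 days, and 13/56 = 0.23 of the access period.

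**iCBT-UP modules completed before t2**

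At one module per week, Module k occupies days 7(k − 1) + 1 to 7k. Each week of delay adds 7 days. The delays are scenarios; the protocol gives no distribution of pace.

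| Pace | Module 5 | Module 6 | Done before t2 |
|---|---|---|---|
| As recommended | days 29–35 | days 36–42 | 6/6 = 100% |
| One week behind | days 36–42 | days 43–49 | 5/6 = 83% |
| Two weeks behind | days 43–49 | days 50–56 | 4/6 = 67% |

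Both delayed schedules fit within the 56 days of permitted access.

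**Which harm sources reach this late work**
- Coded self-report question: no, because it is asked only at t2.
- Questionnaire deterioration: yes, if the worsening is on a scale in Table 3 and is still present at t3. Not if it has resolved by then or is of a kind the scales do not measure.
- Weekly chat and crisis pathway: possibly. The text does not say whether weekly contact continues in weeks 7 and 8, and it does not describe chat reports as coded with the checklist.

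**Effect of repeating the question at t3**
- Access time after the last coded question falls from 13 days to 0.
- Recall window: 72 − 43 = 29 days, of which 72 − 56 = 16 (16/29 = 55%) fall after access has ended.

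**The case against.** The strongest reply is that this is a deliberate and consistent schedule. The Adverse events section, the Governance section and Table 3 all agree on one post-treatment question, and it is paired with a second route through the questionnaires. That stands: there is no contradiction here, and asking again at t3 is an improvement rather than a correction of an error.

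Second, the gap is narrow. The t3 scales, the chat function, crisis support and the trial management group's oversight of adverse events all remain. A reader might infer from the single mark in Table 3 that harm in weeks 7 and 8 is unmonitored. The protocol does not support that. What is lacking is a coded answer for that period, and only effects that resolve by t3 or fall outside the scales would depend on it.

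Third, a reader might infer that coded effects will be undercounted in iCBT-UP, or unequally between arms. The protocol does not show this either. It does not say how many people work after day 43 or what the two extra weeks of access are for; they may serve review rather than catching up. The explicit own-pace sentence appears only for iCBT-UP, although iPMR has the same 8-week access.

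Fourth, day 43 is not the only possible reading. Table 3 refers to the end of the intervention, and Study design dates the follow-up from finishing treatment. If t2 followed each user's own last module, the 13 days would shrink to 0 for those who finish. Day 43 is the better reading because Study design ties t2 to the 6-week programme or waiting period, the final diary week is on fixed days, and the waiting list has no completion date of its own.

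**Conclusion.** The point holds as a minor, conditional one. The only checklist-coded negative-effects question is scheduled about 13 days before access ends, and an iCBT-UP user who is behind may do sensation induction or emotion exposure after it. Negative effects of that work that resolve by t3, or that the symptom scales do not measure, may not be recorded by this question.

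The size is known in days and modules (13 of 56 access days; one or two of six modules in the scenarios shown) but not in people. The conclusion assumes that t2 follows the 6-week calendar and that some users take up the permitted slower pace. Users at the recommended pace lose nothing.

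**What to change.** Repeat the question on the existing t3 form for both active arms. Keep its structure, but limit the period to the time since the last assessment and ask about negative effects from using the programme, with the same request for details. Add the t3 mark in Table 3, amend the Adverse events section to match, code the answers with the same checklist, and report t2 and t3 answers separately by arm. The t2 item and its data stay as they are.

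The cost is one item on an existing online form and a little more coding. There are four downsides:
- Burden rises slightly, and the Discussion already names burden as a concern.
- Recall covers about 29 days, 16 of them after access has ended. Tying the wording to programme use should limit unrelated reports.
- The t3 answers have no waiting-list comparator, because Study design schedules t3 for the active arms only.
- Users who are behind may also be those who miss t3, so the added item may not reach all of the people it is meant for.

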### Risk management

Internet interventions used in the present study were not designed to provide crisis support for persons experiencing suicidal crises. We will exclude individuals with suicidal ideations and refer them to adequate services. We will also monitor participant mood using daily diary measures during the first and last week of the intervention and weekly throughout the intervention, by contacting participants through a chat function to assess any risk. In instances of crisis, we will organise a meeting with our team of psychotherapists and provide crisis support or refer the individual to an adequate service (psychotherapy, psychiatrist, or hospital).

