**Assessments:**							
***MINI***	X						
***IADQ***	X					X	X
***PHQ-9***	X					X	X
***GAD-7***	X					X	X
***SWLS***			X			X	X
***AAS***			X			X	X
***PSS-10***			X			X	X
***FFMQ-15***			X			X	X
***AAQ-II***			X			X	X
***SCS-SF***			X			X	X
***CFQ***			X			X	X
***PTQ***			X			X	X
***WEMWBS***			X			X	X
***Daily diaries***				X	X		
***Cognitive task***			X			X	X
***Adverse events***						X	

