### Sample size calculation

The sample size was determined in relation to the between-group effect size and calculated using G*Power software. Previous research on an online UP intervention and online interventions for AjD has revealed a between-group effect size at the level of *d* = 0.5 and a within-group effect size at the level of *d* = 0.63 [42, 87]. Assuming an alpha 0.05 with a power of 0.80 and post-treatment between-group effect size of *d* = 0.5 (iCBT-UP versus control), 190 participants in the three groups will be sufficient to detect assumed differences. However, because the literature reveals dropout rates from online CBT interventions, with minimal guidance, of approximately 30% [88], a total sample of 247 participants will be recruited.

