### Governance and oversight of the trial

We will establish a trial management group (TMG) that will oversee the whole process of the research—recruitment of participants, assessments, ethical issues, adverse events, and data management. This group will meet once a week during the active phase of the research and in every case as the need arises. The group will consist of the principal investigator, the supervisor and co-principal investigator, and the trial platform manager. Due to the latest recommendations, adverse events will be investigated twofold. First is using our questionnaire outcome measures—to determine the number of patients who deteriorated and those who did not respond to the treatment. Second is using a self-report measure to detect adverse events administered post-treatment (described above) [85]. In case of any changes to the protocol, the TMG will communicate them to the investigators and participants and record them in the study diary.

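### The self-report negative-effects item is asked only at t2 and refers to treatment, so it misses participants lost before t2 and gives no interpretable waiting-list rate

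*Protocol article*

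**What the plan says.** The Adverse events section fixes both the timing and the wording of the item. On timing: "Post-treatment, adverse events will be assessed using a self-reported question". On wording, it asks "Did you experience any negative effects during treatment" and invites further details if the answer is yes. Answers are then coded with a cited checklist of unwanted effects.

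Table 3 agrees. The adverse-events row has a single mark, at t2, which the table defines as "1 day after the intervention". There is no mark during the six weeks or at the one-month follow-up (t3).

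Governance and oversight of the trial describes two routes to adverse events. One is the outcome questionnaires, used to count participants who deteriorated or did not respond. The other is this item: "using a self-report measure to detect adverse events administered post-treatment".

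Three other sections matter:

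- **Waiting List Control (WLC)** has this arm complete the post-treatment assessment before it gains access to a programme. No separate wording of the item is given for it.
- **Risk management** provides for mood checks by diary in the first and last week and "weekly throughout the intervention, by contacting participants through a chat function to assess any risk". Study design adds weekly mood emails for the waiting list. None of these contacts is described as a source of adverse-event data.
- **Sample size calculation** expects dropout "with minimal guidance, of approximately 30" per cent.

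**The concern.** A harm item put once, at the end, reaches only those still in contact at the end. If some participants leave because the programme made them feel worse, the item cannot show it. The questionnaire route does not fill the gap: Table 3 schedules no outcome questionnaire between baseline and t2, so a person lost before t2 and not recovered at t3 contributes an observed value to neither route. Withdrawal is allowed at any moment, and the article describes no harm question at that point.

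The wording causes a second loss. The waiting list is there to separate the effect of the intervention from the passage of time. Students with an adjustment disorder may feel worse over six weeks without any programme, so a background rate is needed to interpret the rates in the active arms. A question about effects of a treatment that the person has not received does not supply one.

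At stake is whether the trial can give a credible rate of self-reported negative effects for a programme meant to be scaled up.

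**Working it through.** The protocol states no adverse-event rate and no target for one, so there is no figure of its own to reproduce. The check is of who can be counted and how far that could move a rate.

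**Who is reached by each source**

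| Participant | Self-report item | Questionnaire deterioration |
|---|---|---|
| Stops the programme, completes t2 | Asked | Observed |
| Lost before t2, returns at t3 (active arms) | Not asked | Observed at t3 only |
| Lost before t2 and not recovered | Not asked | Not observed |
| Waiting list, completes t2 | Asked, but the wording does not apply | Observed, comparable with the active arms |

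**How many may be missed**

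Inputs: N = 247 (Sample size calculation) or 214 (Abstract; the two figures disagree); dropout 30% (Sample size calculation); allocation 2:2:1, so 80% of participants are in the two active arms (Randomization and blinding). Assumption: dropout means missing t2 and is equal across arms.

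- Not asked, all arms: 247 × 0.30 = 74.1, about 74. With the abstract's figure: 214 × 0.30 = 64.2, about 64.
- Active arms: 247 × 0.80 = 197.6, about 198 participants; 197.6 × 0.30 = 59.3, about 59 not asked.
- Left to answer the item: 247 × 0.40 × 0.70 = 69.2, about 69 per active arm; 247 × 0.20 × 0.70 = 34.6, about 35 on the waiting list, where the wording does not apply.

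**What this could do to the rate**

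True rate = 0.70 × (rate in respondents) + 0.30 × (rate in those lost). The 10% in respondents and the multiples for those lost are assumptions; the documents give neither.

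- Same rate (10%) in those lost: 0.70 × 10% + 0.30 × 10% = 10%
- Twice (20%): 0.70 × 10% + 0.30 × 20% = 13%
- Three times (30%): 0.70 × 10% + 0.30 × 30% = 16%

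The item would show 10% in every case. With no excess among those lost there is no bias, and the data collected could not tell these cases apart.

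**Timing**

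The Interventions section gives eight weeks of access and the programme may be taken at the participant's own pace, while t2 follows the six-week period. The modules on physical sensations and emotion exposure come last. A slower user may reach them after the only harm question, which is a further reason to ask again at t3.

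**The case against.** Several stronger readings are tempting, and the protocol does not support them.

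- *That everyone who drops out is never asked.* Stopping the programme is not the same as missing t2. Data analysis keeps those who stop treatment in the intention-to-treat set, and nothing bars them from t2. Only those lost to t2 are missed.
- *That harm cannot be compared with the waiting list at all.* The questionnaire route gives a deterioration rate at t2 in all three arms, and the relaxation arm receives the same item. The comparison gap is confined to one item in one arm.
- *That half or more will be missed.* The Introduction cites dropout of 50–80% in earlier online studies of adjustment disorder. Applied to 247 it would give about 124 to 198 people, but it is dropout during the intervention in other studies, not non-response at t2 here.
- *That the reported rate will be too low.* This needs an excess of harm among those lost. The protocol gives neither reasons for dropout nor a harm rate in that group.

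The case against goes further. Multiple imputation and sensitivity analyses for data not missing at random are planned and could be applied to questionnaire deterioration. That stands in part: imputed scores are not observed harms, and answers to an open question cannot be recovered that way.

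It can also be said that weekly contact takes place in every arm, that a management group meeting weekly oversees adverse events, and that the logging of such contacts may be set out in a full protocol not shown. The article's silence on logging is therefore not a fault in itself. However, it does state the wording and timing of the item, and the finding rests on those. Finally, a cited item and checklist are being used, and more questions add to a burden that the Discussion already links to adherence. That is a fair reason to keep the addition small.

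**Conclusion.** The point holds in limited form. As stated, the self-report item is asked once, at t2, in words that presume treatment. It misses anyone lost before t2 and yields no interpretable waiting-list rate. Because the article fixes both wording and timing, this is a weakness of design and not a detail left to another document.

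Its size rests on assumptions: about 74 of 247 not asked (64 of 214) if 30% dropout means missing t2 equally in all arms, and a true rate of 10–16% behind an observed 10% if those lost have one to three times the respondents' rate. The safe conclusion is that the rate *may* be too low and that the design cannot show whether it is. Questionnaire deterioration remains comparable across arms among those who return. The change is worth making before recruitment, because answers from lost participants cannot be recreated later.

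**What to change.** 1. Reword the item so that it applies to every arm, for example: *Since the start of the study, have you experienced any negative effects? If so, please describe them.* Use it in all three arms at t2, and again at t3 in the active arms, which are the ones followed to that point.
2. Add one recorded negative-effects item to the weekly contact that each arm already receives, and state that the answers count as adverse-event data.
3. Send the same item once when a participant withdraws or becomes inactive.
4. Report by arm the number randomised, the number asked, the number not reached and the number reporting effects, so that the reader can see how much of each rate is unobserved.
5. Update the adverse-events row of Table 3 and the Governance section to match.

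The cost is a change of wording, one short item in messages already sent, some extra coding of open answers and slightly more response burden. No treatment, visit or outcome measure changes.
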